## Abstract

**Background::**

The purpose of this experiment is to evaluate the impact of the care of Parkinson disease nurse specialist on improving motor symptoms and life quality for patients with Parkinson disease (PD).

**Method::**

This is a randomized controlled research, and it will be conducted from April 2021 to October 2021 at Sichuan Provincial People's Hospital. The experiment was granted through the Research Ethics Committee of Sichuan Provincial People's Hospital (004510293). All the patients suffer from PD, age 18 years or older, both female and male, regardless of the duration or severity of this disease are eligible. The exclusion criteria contains: lack sufficient knowledge to complete questionnaires, serious physical comorbidities or refuse to take part in the program. In our experiment, the major result measures are motor symptoms and life quality. For the measurement of life quality, we will utilize Parkinson disease Questionnaire-39, the most extensively utilized the scale of life quality in PD. The evaluation of motor symptoms severity is carried out with the revision of Unified Parkinson Disease Rating Scale sponsored by Movement Disorder Society.

**Results::**

Table 1 indicates clinical outcomes at different time points.

**Conclusion::**

The Parkinson's disease nurse specialist care may promote the life quality in the PD patients.

**Trial registration number::**

researchregistry 6284.

## Introduction

1

Parkinson disease (PD) is a type of progressive chronic neurodegenerative disease, and it is characterized via the apparent dopaminergic neurons early death.^[1,2]^ It is the most prevalent movement disorder, and is the second most familiar central nervous system degenerative disease.^[3]^ PD is also related to the non-motor symptoms, which may be more than a decade earlier than the motor symptoms.^[4]^ In the later stages of PD, such non-motor symptoms can become troublesome. Several researches have reported epidemiological data on PD. Nevertheless, the differences in research methods make it difficult to compare the prevalence estimates directly. It is commonly believed that the incidence of this disease is between 1 and 2/1000 among the unselected population and that 1 percent of population over 60 years of age suffer from PD.^[5,6]^ PD is rare before 50 years old, and in highest age group, the incidence rate is 4%. At present, the main treatment for PD is pharmacological therapy^[7]^; nevertheless, these symptomatic therapies have great limitations for patients with advanced disease. Many disabling characteristics occur later in this disease, involving motor complications after the long-term dopamine treatment, dopamine-resistant motor symptoms, and non-motor symptoms. Despite significant progress has been made in the surgical treatment and medical treatment of PD, there is still a lack of definitive disease-modifying treatment.

More and more studies have emphasized the important role of nursing care in patients with PD.^[8–10]^ In the area of primary health care, the enhanced collaboration between nurses and doctors could result in more comprehensive and therefore better-quality health care. In view of the special PD situation, Parkinson disease nurse specialist (PDNS) may have a significant effect in a team with multidisciplinary.^[11]^ However, PDNS care seldom been used in the care of patients with PD. Therefore, we perform this randomized controlled research protocol to evaluate the influence of the care of PDNS on improving motor symptoms and life quality for the PD patients.

## Methods

2

The experiment will be implemented from April 2021 to October 2021 at Sichuan Provincial People's Hospital. The experiment was granted through the Research Ethics Board of Sichuan Provincial People's Hospital (004510293) and recorded in research registry (researchregistry6284).

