## Result

3

Table 1 indicates clinical outcomes at different time points.

**Table 1 T1:** Clinical outcomes at different time points.

Outcomes	Study group (n = 45)	Control group (n = 45)	*P* value
Quality of life at 6 mo			
Quality of life at 12 mo			
Motor symptoms at 6 mo			
Motor symptoms at 12 mo			
Self-management 6 mo			
Self-management 12 mo			
Total medical cost			

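### The stated trial period of April to October 2021 cannot contain the 12-month outcomes in Table 1, and allows a 6-month outcome only for patients enrolled in April 2021

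*Protocol article*

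**What the plan says.** The protocol article gives one set of dates, twice. Section 2 (Methods) says "The experiment will be implemented from April 2021 to October 2021". The Method paragraph of the Abstract says "it will be conducted from April 2021 to October 2021 at Sichuan Provincial People's Hospital". In both places the dates are attached to the study as a whole. No separate recruitment period, follow-up period or rate of enrolment is given.

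Section 2.4 (Outcome measures) names motor symptoms and quality of life as the major outcomes but sets no time point for them. The times appear only in the empty Table 1 of section 3, under columns headed with 45 patients per group. Three of its seven rows are at 12 months: "Quality of life at 12 mo", "Motor symptoms at 12 mo" and "Self-management 12 mo". Three more are the same outcomes at 6 months, for example "Quality of life at 6 mo". The seventh row, total medical cost, carries no time. Section 2.1 (Randomization) sets the sample at 45 patients per group.

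**The concern.** A study that lasts about seven months cannot contain a visit twelve months after enrolment. The dates and the table are both explicit statements in the same article, and they cannot both be followed. Two of the three 12-month rows are the major outcomes.

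The practical risk depends on which statement the study team follows. If it stops in October 2021, it has no 12-month data, and the number of patients with 6-month data depends on how fast they were enrolled. If it continues in order to fill Table 1, it runs past its stated end. Because section 2.4 fixes no time point for the major outcomes, the choice between 6 and 12 months could also be settled after data have been seen.

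**Working it through.** **Inputs**

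- Period: April to October 2021 (Abstract; section 2). No days of the month are given, so I take the widest reading, 1 April to 31 October 2021.
- Assessment times: 6 and 12 months (Table 1, section 3). I count them from enrolment.
- Sample: 45 + 45 = 90 patients (section 2.1; column heads of Table 1).
- Accrual pattern: not stated. Where one is needed below, it is an assumption.

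The plan gives no figure of its own to reproduce here, so the check is calendar arithmetic.

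**Length of the period.** 30 + 31 + 30 + 31 + 31 + 30 + 31 = 214 days inclusive. With 30.4375 days per month, 214 / 30.4375 = 7.03 months.

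**Rule.** A visit at month m fits only if enrolment date + m months falls on or before 31 October 2021.

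**Month 12.** The earliest enrolment is 1 April 2021, and 12 months later is 1 April 2022. From 31 October 2021 to 1 April 2022 is 30 + 31 + 31 + 28 + 31 + 1 = 152 days. The number of feasible enrolment days is 0, so 0 of 90 patients can have a 12-month value inside the period. This needs no assumption about accrual or dropout.

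**Month 6.** A patient enrolled on 30 April reaches month 6 on 30 October 2021, which fits. A patient enrolled on 1 May reaches it on 1 November 2021, which does not. The feasible enrolment dates are therefore 1 to 30 April, that is 30 of 214 days, or 14%.

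**How many patients that could be.** If accrual were even over the first d days from 1 April, the number able to reach month 6 would be 90 × 30 / d, for d of at least 30:

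| Assumed accrual period | d (days) | 90 × 30 / d | Patients able to reach month 6 |
|---|---|---|---|
| April only | 30 | 90.0 | 90 |
| 2 months | 61 | 44.3 | about 44 |
| 3 months | 91 | 29.7 | about 30 |
| 4 months | 122 | 22.1 | about 22 |
| 6 months | 183 | 14.8 | about 15 |
| 7 months | 214 | 12.6 | about 13 |

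Enrolling all 90 in April would need 90 / 30 = 3 patients per calendar day.

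**If the dates mean recruitment.** A patient enrolled on 31 October 2021 would reach month 12 on 31 October 2022. All the Table 1 times could then be reached.

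**The case against.** The strongest reply is that April to October 2021 is loose wording for the recruitment period in a condensed article. These are the only dates in the text, and on that reading the 12-month rows are feasible and the fault is one badly worded sentence used twice. This stands as a possibility, and the authors' intention cannot be known from the article. It does not remove the problem. Both sentences date the conduct of the whole study, nothing says that follow-up continues after October 2021, and if recruitment was meant, the trial period is misstated. A conflict between two stated facts is also different from detail that an article may leave to the full protocol.

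Three stronger readings are tempting, and the article does not support them.

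- A reader might infer that few patients can reach 6 months. That depends on accrual, which is not given. The low figure of about 13 of 90 assumes even enrolment to the last day, an unlikely plan for a trial with a 6-month visit. What is certain is only that the patient must have been enrolled in April.
- A reader might take Table 1 to require a value from all 45 patients per group at each time. The column heads repeat the group size from section 2.1 and do not say that.
- A reader might conclude that the registry and ethics records carry wrong dates. The article gives only their reference numbers, so no misalignment is shown.

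**Conclusion.** The contradiction holds as written and must be resolved. On the stated dates no patient can supply the three 12-month rows of Table 1, two of which concern the major outcomes. This rests only on reading the dates as the article words them, as the period of the whole trial, and on counting months from enrolment. No other part of the article reconciles the dates with the table.

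The 6-month rows are a question of feasibility, not a contradiction. They are open only to patients enrolled in April 2021, which could be anything from about 13 of 90 (even accrual over 7 months, assumed) to all 90.

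**What to change.** In the Abstract and in section 2, state the recruitment period and the follow-up period separately, and make them agree with the times in Table 1.

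- **If April to October 2021 is recruitment:** say so, and add that 12-month follow-up runs to the end of October 2022, with data cleaning and analysis after that. The cost is two reworded sentences and a later stated completion date.
- **If October 2021 is truly the end of follow-up:** remove the three 12-month rows from Table 1, because they cannot be reported, and limit the 6-month rows to patients enrolled by the end of April 2021. This is not a small change. The 12-month outcomes are lost, and keeping all 90 patients in the 6-month rows would need about 3 enrolments per calendar day throughout April.

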### Randomization

2.1

This is a randomized controlled trial. Sequence of random numbers is generated by a computer. Sequentially numbered sealed opaque envelopes are used for the concealment of random numbers. All the patients participating in this study are randomly divided into control group and intervention group, with 45 patients in each group.

### Inclusion and exclusion criteria

2.2

All the patients suffer from PD, age 18 years or older, both female and male, regardless of the duration or severity of this disease are eligible. The exclusion criteria contains: lack sufficient knowledge to complete questionnaires, serious physical comorbidities or refuse to take part in the program.

### PDNS intervention

2.3

Intervention of PDNS will be implemented on the basis of the guideline of “Nursing care in PD”, which was issued in 2015. This involves the following:

(1)Evaluation of the individual nursing needs of PD patients and the patients’ caregivers: At the beginning of this research, PDNS conducts the specific nursing evaluations associated with the social, psychological, physical, and medical fields.(2)Develop a treatment plan centered on patients to support the self-management of patients and their caregivers: PDNS forms a multidisciplinary program on the basis of the individual evaluation results and in accordance with the priorities of patients and caregivers.(3)The specific nursing intervention: the intervention measures are different in disease stages, and the specific requirements and the problems of the individual patients and the patients’ caregivers are adjusted. The guideline of “Nursing care in PD” describes the specific measures and general measures for the interventions of nursing. The general measures of interventions involve providing relevant education and information, the treatment and monitoring of disease. While the specific nursing interventions contain the psychological function, urogenital function, sexual behavior, sleep, fatigue, orthostatic hypotension, the medication compliance, the burden of caregiver, self-management, mobility, coping, and the dietary problems.(4)The collaboration with other professionals of health care. PDNS encourages and supports the multidisciplinary collaboration among the professionals of health care on the basis of the individual treatment program. The PDNS also possesses a significant effect in referral to some other health professionals in time. While the control group patients are given conventional nursing care.

### Outcome measures

2.4

In our experiment, the major result measures are motor symptoms and life quality. For the measurement of life quality, we will utilize Parkinson disease Questionnaire-39,^[12]^ the most extensively utilized the scale of life quality in PD. The evaluation of motor symptoms severity is carried out with the revision of Unified Parkinson Disease Rating Scale sponsored by Movement Disorder Society.^[13]^

### Statistical analysis

2.5

By using Microsoft Excel 2013, the data are recorded, and the analysis of all the data is carried out through utilizing the software of IBM SPSS Statistics for Windows, version 20 (IBM Corp., Armonk, NY). And the data are represented via the proper characteristics, for instance, median, mean, and percentage. The categorical variables and continuous variables are respectively analyzed applying the *χ*^2^-tests and independent *t*-tests. When *P* < .05, the efficacy is viewed to be statistically significant.

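### The stated t-tests make no use of the baseline score: valid under randomization, but less precise than ANCOVA and exposed to whatever chance imbalance occurs

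*Protocol article*

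**What the plan says.** - **Test.** Section 2.5 (Statistical analysis) has one sentence on method: "The categorical variables and continuous variables are respectively analyzed applying the *χ*^2^-tests and independent *t*-tests". It names no covariate, change score or model.
- **Outcomes.** Section 2.4 (Outcome measures) states that "the major result measures are motor symptoms and life quality", measured by PDQ-39 and by the Movement Disorder Society revision of the UPDRS.
- **What is compared.** The Table 1 shell in section 3 (Result) has rows such as "Quality of life at 6 mo", with 6- and 12-month rows for quality of life, motor symptoms and self-management. Each row has one column per group and a P value. There is no row for baseline or for change.
- **Who enters.** Under section 2.2 (Inclusion and exclusion criteria), adult patients "regardless of the duration or severity of this disease are eligible".
- **Allocation.** Section 2.1 (Randomization) says "Sequence of random numbers is generated by a computer", "with 45 patients in each group". It mentions no stratification by severity or by baseline score.

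**The concern.** Both main outcomes measure disease burden, and the entry criteria let that burden vary widely between patients on the day they enter. Part of the spread in follow-up scores will therefore already be present at baseline. An unadjusted t-test treats all of that spread as noise, while an analysis with the baseline score as covariate removes the part that baseline predicts.

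Two things are at stake. First, with 45 patients per arm, power is given away that one extra covariate would recover. Second, the arms may differ at entry by chance. Nothing in the stated allocation limits that difference, and nothing in the stated analysis corrects for it once it has occurred. These are two views of one loss: averaged over all possible randomizations, the imbalance is already inside the t-test's standard error, but the realised imbalance still affects how the one trial actually run should be read.

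**Working it through.** **Inputs from the document:** 45 per group (section 2.1); independent t-test with threshold P < .05 (section 2.5).

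**Assumptions, not in the document:** a two-sided test; equal SD at baseline and follow-up, set to 1; complete follow-up; baseline to follow-up correlation r between 0.3 and 0.8; a true effect of 0.5 SD, for illustration only.

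The 45 per group is given without effect size, SD, power or dropout. It cannot be reproduced, so it is taken as it stands.

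**Step 1: the planned t-test.** The standard error of the difference is √(2/45) = 0.211 SD.
- Detectable with 80% power, normal approximation: (1.960 + 0.842) × 0.211 = 0.59 SD. Exact noncentral t: 0.597 SD.
- Power for 0.5 SD: 66% by normal approximation, 65.0% by exact t.

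**Step 2: ANCOVA on the baseline score.** The residual variance is multiplied by 1 − r². The detectable difference becomes 0.597 × √(1 − r²). The t-test sample size giving the same precision is 45/(1 − r²). Power is from the noncentral t with one degree of freedom fewer.

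| Assumed r | Variance factor 1 − r² | Reduction | Detectable at 80% power | Power for 0.5 SD | Equivalent t-test n per arm |
|---|---|---|---|---|---|
| t-test as planned | 1.00 | none | 0.597 SD | 65.0% | 45 |
| 0.3 | 0.91 | 9% | 0.57 SD | 69.1% | about 50 |
| 0.5 | 0.75 | 25% | 0.517 SD | 77.3% | 60 |
| 0.7 | 0.51 | 49% | 0.426 SD | 90.7% | about 88 |
| 0.8 | 0.36 | 64% | 0.358 SD | 97.4% | 125 |

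**Step 3: chance imbalance at entry.** The baseline difference between arms has the same standard error, 0.211 SD. The probability of an imbalance larger than 0.2, 0.3 or 0.4 SD, in either direction, is 34%, 15.5% and 6%.

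An imbalance b shifts the unadjusted follow-up difference by r × b. For r = 0.7 and b = 0.3 SD, that is 0.7 × 0.3 = 0.21 SD, about one standard error. Given that imbalance, with z denoting a standard normal variable, the type I error of the t-test is

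P(z > (1.96 − 0.21/0.211)/√0.51) + P(z < (−1.96 − 0.21/0.211)/√0.51) ≈ 9%.

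For b = 0.4 SD it is about 19%. With perfect balance (b = 0) it is about 0.6%. These conditional rates average to the nominal 5% over all randomizations.

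**Step 4: if change scores were meant.** The variance of a change score, relative to a follow-up score, is 2(1 − r): 1.4, 1.0, 0.6 and 0.4 at r = 0.3, 0.5, 0.7 and 0.8. The ANCOVA factors are 0.91, 0.75, 0.51 and 0.36, smaller in every case. Below r = 0.5 a change score is less precise than the follow-up score alone.

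**The case against.** The strongest reply is that nothing here is invalid. Allocation is by computer-generated numbers in sealed opaque envelopes, so the unadjusted t-test is unbiased and keeps its overall 5% error. That stands, and several stronger readings fall with it or for related reasons:

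- **Bias.** A reader might infer that the result will be biased by baseline differences. The document does not support this. The imbalance is random, and the conditional error rates above describe particular realised imbalances.
- **Raw scores as a stated choice.** Section 2.5 does not say whether scores or changes are tested. That follow-up scores are meant is inferred from the Table 1 labels. Step 4 shows that ANCOVA is more precise in either case.
- **Follow-up scores mostly determined by baseline.** Baseline explains r² of the follow-up variance, and this exceeds one half only if r is above about 0.71. The document gives no r. At r = 0.3 the gain is only 9% of variance, and 125 per arm with 97% power is the top of the assumed range.
- **No baseline measurement.** Table 1 is an outcome shell, and a condensed article may leave baseline tables and visit schedules to the full protocol. The absence of a baseline row does not show that baseline is not collected.
- **A table with nothing but P values.** The shell also has a column for each group, and section 2.5 promises means, medians and percentages. A missing interval column in an article's shell is not in itself a defect.

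What remains is that section 2.5 names the test. This is a stated choice, not a detail left for later, and a more precise method is available.

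**Conclusion.** The point holds as one about efficiency. The stated test is legitimate, but it leaves the baseline score unused in a small trial with unrestricted disease stage and no described stratification. For r between 0.3 and 0.8 the cost runs from slight (9% of variance, 4 points of power) to large (64% of variance, 32 points of power). In addition, about one randomization in six or seven would give an entry imbalance of 0.3 SD or more, which the planned comparison would carry into the estimate in proportion to r. The sizes rest on the assumed r and on the other assumptions listed; the direction does not, because over this whole range ANCOVA gains precision for one degree of freedom. This is a cheap, worthwhile improvement. It does not make the planned analysis wrong.

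**What to change.** 1. State that PDQ-39 and MDS-UPDRS are measured in both arms before allocation, if this is not already planned.
2. In section 2.5, replace the t-tests on these scores with ANCOVA: follow-up score on arm plus the baseline value of the same score, at each visit actually held.
3. Report the adjusted between-group difference with its 95% CI beside the P value in Table 1.
4. Reconcile the 12-month rows of Table 1 with the April to October 2021 period in section 2 (Methods) before specifying any model that spans 6 and 12 months. The 6-month ANCOVA does not need a 12-month visit.

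The cost is one baseline administration of instruments already in use, one degree of freedom per model and a few lines of text. No extra patients are needed, and the statistical package already named can fit ANCOVA. Make the change before enrolment: a baseline taken before allocation cannot be recovered later, and a covariate chosen after seeing the data is less credible.

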## Conclusion

5

The PDNS care may promote the life quality in the PD patients.

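### Two unranked major outcomes at two time points share an unadjusted P < .05 rule: if any one test suffices, the false-positive rate is well above 5%

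*Protocol article*

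**What the plan says.** Section 2.4 of the protocol article (Outcome measures) states: "In our experiment, the major result measures are motor symptoms and life quality". Quality of life is measured with the PDQ-39 and motor symptoms with the MDS-UPDRS. The section does not order the two or attach a time point to either.

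Table 1 in section 3 (Result) has a P value column. Each major outcome appears there twice, at 6 and at 12 months, for example "Quality of life at 6 mo" and "Motor symptoms at 6 mo". Three further rows cover self-management at the same two times and total medical cost.

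Section 2.5 (Statistical analysis) says that variables are "analyzed applying the *χ*^2^-tests and independent *t*-tests". It gives one criterion for all of them: when P is below .05, "the efficacy is viewed to be statistically significant".

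The Abstract and section 2 place the study between April and October 2021. Section 2.1 assigns 45 patients to each group. Section 5 (Conclusion) mentions quality of life only: "The PDNS care may promote the life quality in the PD patients".

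**The concern.** Read together, sections 2.4, 2.5 and Table 1 give four between-group tests on major outcomes and one unadjusted threshold at which efficacy is called significant. They contain no rule for turning four P values into one answer about the trial. A success on one outcome at one time could be presented as a positive trial, and so could a success on both.

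Two things are at stake. If one success is enough, the 5% level applies to each test and not to the trial's claim. And if the deciding outcome and time are not fixed beforehand, they can be chosen after the results are known, so a reader cannot tell a planned success from the best of four. The difference in emphasis between section 2.4 (both outcomes) and section 5 (quality of life only) shows how easily the focus could move.

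**Working it through.** **Inputs from the protocol article**
- Threshold: .05 (section 2.5). Sidedness is not stated; two-sided is assumed.
- Major outcomes: 2 (section 2.4).
- Time points per major outcome: 2 (Table 1), so 2 × 2 = 4 tests.
- Group size: 45 per arm (section 2.1).
- Study period: April to October 2021 (Abstract, section 2).

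**Assumed, because the document gives no figure**
- Correlation of the test statistics: 0.5 to 0.9 between time points and 0.2 to 0.6 between outcomes.

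**Step 1. The plan's own figure.** For one test, 1 − 0.95 = 0.05. The stated level is correct for a single test.

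**Step 2. Four tests, any one sufficient, no true effect.**
- Independent: 1 − 0.95^4 = 1 − 0.8145 = 0.1855, which is 0.1855 / 0.05 = 3.7 times the stated level.
- Upper bound under any dependence: 4 × 0.05 = 0.20.
- Correlated: simulation of four normal statistics, 1,000,000 draws, two-sided critical value 1.96:

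| Between times | Between outcomes | At least one P < .05 | Ratio to .05 |
|---|---|---|---|
| 0.5 | 0.2 | 0.172 | 3.4 |
| 0.7 | 0.3 | 0.156 | 3.1 |
| 0.8 | 0.5 | 0.140 | 2.8 |
| 0.9 | 0.6 | 0.122 | 2.4 |

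Counting only results that favour the intervention, against a one-sided .025, gives nearly the same ratios.

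**Step 3. One time point, two tests, either sufficient.** April to October 2021 spans at most seven months, so a 12-month outcome cannot be reached within it. If only one time point remains:
- Independent: 1 − 0.95^2 = 1 − 0.9025 = 0.0975, or 1.95 times .05.
- Correlation 0.3: 0.095. Correlation 0.5: 0.091. Correlation 0.7: 0.084.

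**Step 4. Both outcomes required at one time point.** A false joint claim needs every ineffective outcome to reach P < .05. Its probability therefore cannot exceed 0.05, and no adjustment is needed.

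**Step 5. What control costs in sensitivity.** The detectable difference in SD units at 80% power is approximately (z for alpha/2 + z for power) × √(2/45), and √(2/45) = 0.211.
- At .05: (1.960 + 0.842) × 0.211 = 0.59; exact t-test calculation 0.60.
- At .025: (2.241 + 0.842) × 0.211 = 0.65; exact 0.66.
- At .0125 (Bonferroni over all four): exact 0.72.

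**The case against.** The strongest reply is that section 2.5 only states the usual per-test threshold. It does not say that one significant row establishes efficacy, and section 2.4 joins the two outcomes with *and*. If both had to succeed, Step 4 shows no inflation. This stands in part. The any-one-suffices rule is permitted by the text but not spelled out, so the size of the problem has to be stated conditionally. It does not remove the point, because no sentence requires joint success either.

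A second reply is that this is a condensed article, and an adjustment method may sit in an analysis plan that is not shown. That is fair as regards the method, and its absence alone would be no finding. But this article does state two unranked major outcomes, P values at two times and an unadjusted criterion. The objection is to that rule as stated.

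Three stronger readings are tempting and are not supported:
- A reader might infer that the error rate simply is about three times the stated level. That ratio depends on correlations the document does not give, on the any-one reading, and on 12-month rows that do not fit the study dates.
- A reader might count all seven rows of Table 1 and arrive at 1 − 0.95^7 = 30.2%. Section 2.4 limits the major outcomes to two, self-management is not among them, and cost is not an efficacy outcome.
- A reader might take section 5 to show that quality of life is the intended primary outcome. It was written with Table 1 still empty and does not rank anything; section 2.4 lists motor symptoms first.

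**Conclusion.** The point holds in conditional form. The document leaves the decision rule undefined across four tests on two major outcomes while fixing an unadjusted .05 for each.

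If any one test suffices, the trial-level false-positive rate is 18.5% with independent tests and about 12% to 17% over the assumed correlations. If the dates leave one time point, it is 9.75% with independence and about 8.4% to 9.5% at correlations of 0.7 to 0.3, roughly twice the stated level. If both outcomes were required at one fixed time point, it would not exceed 5%, but the document does not say so.

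The count of tests and the independence figures follow from the text. The correlated figures rest on assumed values. Which time-point case applies depends on how the conflict between the study period and the 12-month rows is resolved.

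**What to change.** 1. Reconcile the April to October 2021 period with the 12-month rows of Table 1, and name one deciding time point in section 2.4.
2. In section 2.5, state one rule at that time point that keeps the two-sided 0.05 level over the two major outcomes. Any of these would do:
   - Holm over the two outcomes;
   - one outcome named primary and the other tested only if the first is significant (fixed sequence);
   - both outcomes required to be significant, each at .05.
3. Report the other time point, self-management and cost as secondary, with estimates and confidence intervals and no efficacy claim.

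This needs a few sentences and no extra patients, and should be settled before outcome data are seen.

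Each rule has its price. Under Holm, the outcome tested at .025 has a detectable difference of about 0.66 SD instead of 0.60 SD (80% power, 45 per arm); a four-way Bonferroni split would raise it to about 0.72 SD. Under a fixed sequence, the second outcome cannot carry a positive claim alone. Requiring both lowers the chance of success: at a true difference of 0.6 SD on each outcome, power per test is 0.804, and joint power would be 0.804 × 0.804 = 0.65 if independent, higher with positive correlation. Which outcome goes first, if either, is for the sponsor to choose and justify.
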